### Exclusion criteria

The following are the exclusion criteria:
Patients with chronic lung conditionsPatients with chronic kidney diseasePatients affected with chronic neurological disordersPatients suffering from hypertension and cardiovascular conditions without medical treatmentPatients affected with grade III osteoporosisPatients affected with acute phase of rheumatologic disordersPatients affected with acute phase of disc abnormalitiesPatients who have had respiratory conditions in the last 12 monthsPatients who have recent musculoskeletal disorders and who are not fully recovered from their injuriesPatients who have received physical therapy treatment in the last 3 monthsPatients affected with chronic mental and/or psychological disturbancesRed flags for serious conditions (night pain, severe muscle spasm, loss of involuntary weight, symptom mismatch)Patients classified as moderate/severe cases based on the following criteria [33]:
Respiratory rate ≥ 30 brpmSpO2 < 92%Cardiac rate > 125 bpmHypotension (SBP < 90 mmHg or DBP < 60 mmHg)Severe dyspnea (minimal effort or rest)Signs of respiratory compromise (cyanosis, use of accessory muscles)HemoptysisAltered alertness (lethargy, acute confusion, disorientation)Inability to orally intake due to unintended vomiting or a significant number of bowel movements (≥ 10 per day) suggesting dehydration or hydroelectric disturbancesSignificant impact on the general conditionHigh clinical suspicion of pneumonia requiring radiography, based on worsening of dyspnea, more than 7 days with fever, respiratory rate higher than 22 brpm, and alteration in auscultation. Punto 3.

### Interventions

Patients will perform exclusively assigned therapeutic exercises or sedentary activities (depending on randomized allocation to the study groups) and may not combine with other physical therapy or sports physical activity. Any interference in the treatment will be grounds for exclusion, participants will be asked in the daily contacts if they have carried out any activity that can be considered as meddling in the treatment. If participants are required to combine the intervention with medications, it will be registered.

Exercise monitoring will be developed through telerehabilitation tools, that is, emerging technology through which medical rehabilitation care can be provided through a distance. Patients will be encouraged to carry out treatment and follow-up completely, through videoconferences that will encourage them to improve their health status through their personal effort and will reduce the rate of loss to follow-ups and dropouts. In the event that losses to follow-up or dropouts of more than 15% are observed, we will perform an intention-to-treat analysis.

### Group 1: Respiratory exercise program

The REP will consist of 10 exercises based on the recommendations made by the official physiotherapy organizations at the institutional level (College of Physiotherapists of the Community of Madrid, Spain) [34]; with scientific evidence, the method of active cycle of breathing techniques uses an alternate depth of breathing to move mucus from small airways at the bottom of the lungs to bigger airways, where they can be cleaned in an easier way by coughing. In addition, postural changes can modify positively the ventilation/perfusion index [35]. The REP will be taught to patients telematically in the first session, and it will be carried out once a day, for 21 days, at the patient’s home, between 11 a.m. and 12 a.m., in the morning, and is described in Additional file 1. The REP will be reinforced by a physical therapist daily, through telematic control by videoconference with each patient.

### Group 2: Non-specific toning exercise program

The NTEP will consist of 10 exercises based on the recommendations about toning exercises, made by the official physiotherapy organizations at the institutional level (College of Physiotherapists of the Community of Andalusia, Spain) [34]; with scientific evidence, it has been demonstrated that exercise therapy produces many benefits in the immune/defense system. Due to the established relationship between this system and COVID-19 effects, we have decided to include a group of unspecific exercises and to analyze how patients will benefit from this kind of exercises [36, 37]. We also try to avoid physical deconditioning, with the physiological deterioration it implies [16, 17].

The NTEP will be taught to patients in the first session, and it will be carried out once a day, for 21 days, at the patient’s home, between 11 a.m. and 12 a.m., in the morning, and is described in Additional file 1. The NTEP will be reinforced by a physical therapist daily, through telematic control by videoconference with each patient.

### Group 3: Sham program

The sham program consists of 10 sedentary exercises based on sophrology and meditation, with mental exercises of visualization, concentration, and mental activity. The program will not follow a linear progression nor will it have the objective of obtaining benefits through meditation; it will only try to interact with the subjects for an hour. The sham program (SP) will be taught to patients in the first session telematically, and it will be carried out once a day, for 21 days, at the patient’s home, between 11 a.m. and 12 a.m., in the morning. The SP will be reinforced by a physical therapist not specialized in meditation daily, through telematic control by videoconference with each patient. After the study, patients in the SP group will carry out the exercise program that has shown the greatest benefits in the state of health (REP or NTEP), which we consider ethically necessary.

### Procedure for adverse effects

Participants will be daily assessed through a phone call by a member of the study team, who will ask for possible adverse events. This follow-up will be performed through a checklist translated and adapted from “Criteria for clinical evaluation during telephone follow-up of home care” published by SEMFYC [33], and it can be checked in Additional file 2. In addition, a telephone number will be provided to the participants. If any complication or doubt, they should contact the member of the study team, and in the function of episode features, they will be informed of the procedure to follow.

The Trial Steering Committee is made up of three researchers external to the research group; they will meet weekly and analyze the ongoing results of the research; they have the power to partially or completely paralyze the course of the study. This study does not contemplate any intervention of public organisms for its development.

### Outcome measures

The data will be collected by personnel attached to the research group who have previously been instructed in the procedures to follow and do not know the group to which the patients belong; the captures sent by the patients will be stored and classified; the evaluators will transfer the numerical values to an excel table. The images sent by the patients and the excel table are encrypted, and only the evaluators and the main researchers have access to it. This information is updated through a security cloud. All outcomes will be measured daily using WhatsApp or by email for 21 days.
Visual Analog Scale Fatigue (VASF), for fatigue measurement [38]. Patients participating in the study will indicate the intensity of their fatigue by means of the VAS through the smartphone application called “Visual Scale” (Apple Store and Google Play). They will have to signal in a horizontal line where they would place their fatigue, being 0 “no fatigue” and the 10 would be “the worst imaginable fatigue”. VASF will be controlled telematically by the evaluators through the Smartphone application. The evaluator will ask the patient to indicate their level of VASF in the “Visual Scale” application and to take a screenshot of the smartphone to obtain the established value for VASF, which is calculated as the average value of two attempts. The patient must send the VASF screenshot daily to the evaluator, via WhatsApp or email.Forced expiratory volume in 1 s (FEV1). The Piko-1 spirometer device will be sent to the home of each patient by post, and a telematic control of its use will be carried out. The evaluator will ask the patient to indicate their level of FEV1 assessed by the Piko-1 device, twice each time. FEV1 obtained values by patients must be sent to the evaluator, via WhatsApp or email. We will calculate the means of each 2 measurements, assessed by patients every day [39, 40].Peak expiratory flow (PEF). The evaluator will ask the patient to indicate their level of PEF assessed by the Piko-1 device, twice each time. After obtaining the values, patients will send them to the evaluator, via WhatsApp or email. We will calculate the means of each 2 measurements, assessed by patients every day [41].Six-Minute Walk Test (6MWT). The 6MWT will be performed by all patients in their home, under the telematically supervision of a physiotherapist. All patients will receive the same instructions before the walk and will be encouraged by the physiotherapist who repeated set phrases every minute during the walk. The distance covered during the test will be recorded in meters telematically by the patient’s smartphone. Patients will be allowed to stop and rest during the test, but they will be instructed to resume walking as soon as they felt able to do so. Patients will send the results of the 6MWT screenshot daily to the evaluator, via WhatsApp or email [42].Thirty Seconds Sit-To-Stand Test (30STST). Evaluators will ask patients to place a straight-backed armless chair, with a hard seat, which will be stabilized by placing it against a wall, considering floor to seat height will be between 45 and 50 cm. Seated participants will be asked to come forward on the seat until their feet will be flat on the floor and to fold their upper limbs across the chest, without moving it during all tests. Patients will be then instructed to stand up all the way and sit down once without using the upper limbs. Patients will start in the seated position on the chair and, upon command telematically, they will stand up, and then they will return to sitting as many times as they could, in a 30-s time period [41–43]. The evaluators will control this test telematically by videoconference.Multidimensional Dysphnoea-12 (MD12) Spanish version [44]. The MD12 questionnaire will be self-administered and will be performed at the end of the 6MWT. Patients will send the results of the MD12 screenshot daily to the evaluator, via WhatsApp or email.Borg Scale (BS). The Borg Scale, of perceived effort, measures the entire range of effort that the individual perceives when exercising. This scale gives criteria to make adjustments to the intensity of exercise, that is, to the workload, and thus forecast and dictate the different intensities of exercise in sports and medical rehabilitation. The BS will be completed by patients at the beginning of each session and after completing the exercise program, as well as at the end of the tests, every day (6MWT, 30STST). Patients will send the results of the BS screenshot daily to the evaluator, via WhatsApp or email [45, 46].

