## Objectives

### Primary objective

The aim of our study is to analyze the respiratory effects of a therapeutic exercise program in patients affected by the coronavirus (COVID-19), during the period of home confinement.

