### Sampling and sample size calculation

The sampling of our research will be non-probabilistic, since we will contact the patients through social networks, and not the entire population belongs to these networks, so the selection of the sample will be possible only among those who voluntarily respond to our request.

The sample size will be calculated using the Granmo calculator v.7.12, based on the minimum clinically important differences in VASF [43], and estimating an alpha risk of 5% (0.05), a beta risk of 10% (0.10), in a unilateral contrast, a typical deviation of 12.5% (0.125), a minimum difference to detect of 10% (0.10), and a rate of follow-up losses of 15%, for which 32 subjects are required in each group, assuming that there are three groups. If the rate of loss to follow-up were observed greater than 15%, we will perform an intention-to-treat analysis. Finally, we will include 114 patients who will be divided into three groups, each group of at least 38 subjects, being able to overcome this value to assume the possible loss of follow-up.

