### Blinding

Evaluator and patients in the study will be blinded during the entire process. The evaluator will be unaware of the study objectives and the randomized distribution of patients to study groups and will not have access to the randomization sequence. Meanwhile, although blinding for patients will not be possible to achieve it completely, subjects will be unaware of other treatment modalities, and they will not know if they belong to the intervention or sham group.

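### FEV1 and PEF are scored as the mean of two blows, so one poor blow pulls the day's score down; the better blow is a cheap improvement whose benefit depends on how far poor effort is shared between the two blows

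*Protocol article*

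**What the plan says.** The Outcome measures section of the protocol article fixes the number of blows and the scoring rule for both lung-function measures.

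- FEV1: "The evaluator will ask the patient to indicate their level of FEV1 assessed by the Piko-1 device, twice each time".
- PEF: "The evaluator will ask the patient to indicate their level of PEF assessed by the Piko-1 device, twice each time".
- Scoring, stated once for each measure: "We will calculate the means of each 2 measurements, assessed by patients every day".
- Supervision of the posted device: "a telematic control of its use will be carried out". The Sample selection section adds that the evaluator instructs and remotely controls all measurements.
- Frequency: "All outcomes will be measured daily using WhatsApp or by email for 21 days".

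The Primary objective is to "analyze the respiratory effects of a therapeutic exercise program in patients affected by the coronavirus (COVID-19"). FEV1 and PEF are the two direct lung-function measures among seven listed outcomes. The article names no single primary outcome. On patient blinding, the Blinding section concedes that "although blinding for patients will not be possible to achieve it completely".

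**The concern.** FEV1 and PEF have meaning only when the patient blows as hard as possible. A leak, a slow start or an incomplete breath in lowers the reading, so gross error runs mainly in one direction. Averaging suits a self-rating such as the fatigue scale, whose error can go either way and which the protocol also averages over two attempts. In a forced blow the average carries the shortfall of whichever blow was poor, and with only two blows each has half the weight.

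Two things are at stake in the outcomes closest to the respiratory objective. The first is extra measurement noise. The second is that a difference between arms in how often patients blow submaximally, if there is one, would appear as a difference in lung function.

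**Working it through.** **The plan's own figure.** The only computed figure is the sample size, based on fatigue with "an alpha risk of 5% (0.05), a beta risk of 10% (0.10), in a unilateral contrast", SD 0.125 and difference 0.10.

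- n = 2 × (1.645 + 1.282)² × (0.125/0.10)² = 26.8, so 27 per group.
- 27/0.85 = 31.8, so 32, as stated. 32/0.85 = 37.6, so 38, and 3 × 38 = 114.

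It reproduces, and the scoring rule for FEV1 and PEF does not touch it.

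**Inputs.** Two blows per occasion and the mean as score come from the Outcome measures section. The documents give no rate of poor blows, no size of shortfall, no blow-to-blow SD and no correlation of effort between blows. Everything below on those is assumed.

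**Step 1: one poor blow.** With shortfall s on one of two blows, the mean falls by s/2 and the better blow is unchanged. For s = 20% the mean falls by 10%.

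**Step 2: two arms with equal lungs, independent blows.** Let a blow be poor with probability p. The expected loss is s·p for the mean and s·p² for the better blow. The false arm difference is s(pB − pA) against s(pB² − pA²), and the second is smaller whenever pA + pB < 1.

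- s = 20%, 10% against 30%: mean 0.20 × 0.20 = 4.0% of true value; better blow 0.20 × (0.09 − 0.01) = 1.6%.
- Over s = 10-20% and rate pairs 10/20%, 10/30% and 20/40%: mean 1.0-4.0%, better blow 0.3-2.4%.

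**Step 3: simulation in litres.** True FEV1 is 3.0 L. Each blow is 3.0 − |N(0, 0.06)|, multiplied by 1 − U(0.1, 0.3) when submaximal. With independent blows:

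| Submaximal rate | Mean of two: bias, SD (L) | Better of two: bias, SD (L) |
|---|---|---|
| 10% | −0.107, 0.133 | −0.037, 0.059 |
| 20% | −0.166, 0.177 | −0.055, 0.107 |
| 30% | −0.225, 0.204 | −0.083, 0.153 |

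For 10% against 30%, the false difference under the mean is 0.225 − 0.107 = 0.118 L. Under the better blow it is 0.083 − 0.037 = 0.046 L.

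**Step 4: effort shared between the two blows.** Let the second blow copy the first blow's status with probability r. The lower better-blow figure shares only the status; the higher one shares the size of the shortfall as well.

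| r | Mean: false difference (L) | Better blow: false difference (L) |
|---|---|---|
| 0 | 0.118 | 0.046 |
| 0.5 | 0.118 | 0.074-0.082 |
| 0.8 | 0.118 | 0.091-0.104 |
| 1 | 0.118 | 0.102-0.119 |

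The gain from the better blow falls from 0.118 − 0.046 = 0.072 L to about nothing. The noise advantage shrinks too: at a 10% rate and r = 0.8 with the shortfall shared, the SDs are 0.177 L (mean) and 0.171 L (better blow).

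**Step 5: symmetric error instead.** With blow SD σ, the mean has SD σ/√2 and no offset. The better blow has SD σ√(1 − 1/π) and upward offset σ/√π.

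- σ = 0.10 L: SD 0.071 against 0.083 L; offset 0.056 L.
- σ = 0.20 L in one arm and 0.10 L in another: offsets 0.113 and 0.056 L. The better blow then gives a false difference of about 0.056 L, and the mean gives none.

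**The case against.** The rule is complete, reproducible and the same in every arm on every day. It contradicts nothing else in the article and changes no planned number. Any downward offset common to all arms cancels in between-group comparisons. All of this stands, and the point is therefore about a better choice of score, not an error of fact.

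A reader might infer that poor blows will be common because the device is posted to patients who take their own readings. The documents do not support that: measurements are instructed and remotely controlled by an evaluator, and no rate of poor blows is given.

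A reader might also infer that the mean biases the trial towards the respiratory arm, because that arm alone trains breathing. The documents do not show this either. The described content is alternating depth of breathing and postural change, the exercises themselves are in an additional file that is not shown, and every arm makes the same two blows daily for 21 days. Incomplete patient blinding makes a difference in effort possible, but neither its existence nor its direction is shown.

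The strongest technical objection is that tiredness, cough and low motivation act on the patient or the day, so they affect both blows. Steps 4 and 5 bear this out: the gain can vanish when effort is fully shared, and under symmetric error the better blow can create an arm difference that the mean would not.

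**Conclusion.** The point holds as a cheap improvement. The article explicitly fixes the mean for two maximal-effort measures, and under one-sided error the better blow is never materially worse and may be clearly better. At the assumed 10% against 30% submaximal rates and 3.0 L, the false arm difference of about 0.12 L under the mean falls to 0.05 L if effort is independent between blows. It falls to 0.07-0.08 L if half of pairs share effort, and to 0.10-0.12 L if all do.

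These figures rest wholly on assumed rates, shortfalls and correlation, and on error being mainly downward. They illustrate how the two rules behave and do not predict a bias in this trial. Even where effort is equal across arms, the mean is the noisier score when poor blows occur independently (SD 0.133 against 0.059 L at a 10% rate). The better blow reduces the problem but does not remove it, and it does not help when both blows are equally poor.

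**What to change.** Replace the scoring sentence for each measure: the day's FEV1 is the higher of the two FEV1 readings, and the day's PEF is the higher of the two PEF readings. Keep both raw values in the data table, and report the mean of two as a sensitivity analysis. Make the change before any comparison by group is seen.

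The cost is one sentence per measure. Both readings are already taken and sent, so there is no new measurement and no added burden on patients, and the sample size stands.

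The price in the analysis is the one in Step 5: a slightly larger SD if blow error is symmetric, and an upward offset that differs between arms if blow variability does. With both raw values kept, the within-pair spread can be compared across arms, and the sensitivity analysis shows whether the choice of score matters.

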
### Participants’ timeline

A brief Standard Protocol Items: Recommendations for Interventional Trials (SPIRIT) flow diagram is provided in Fig. 1, and a populated SPIRIT checklist is provided in Additional file 3.

**Fig. 1 Fig1:**
[figure not shown]
SPIRIT flow diagram. W, week; REP, respiratory exercise program; NTEP, non-specific tonic exercise program; SP, sham group; VASF, visual analog scale fatigue; FEV1, forced expiratory volume in 1 s; PEF, peak expiratory flow; 6MWT, Six-Minute Walk Test; 30STST, Thirty Seconds Sit-To-Stand Test; BS, Borg Scale; MD12, Multidimensional Dysphnoea-12

### Sampling and sample size calculation

The sampling of our research will be non-probabilistic, since we will contact the patients through social networks, and not the entire population belongs to these networks, so the selection of the sample will be possible only among those who voluntarily respond to our request.

The sample size will be calculated using the Granmo calculator v.7.12, based on the minimum clinically important differences in VASF [43], and estimating an alpha risk of 5% (0.05), a beta risk of 10% (0.10), in a unilateral contrast, a typical deviation of 12.5% (0.125), a minimum difference to detect of 10% (0.10), and a rate of follow-up losses of 15%, for which 32 subjects are required in each group, assuming that there are three groups. If the rate of loss to follow-up were observed greater than 15%, we will perform an intention-to-treat analysis. Finally, we will include 114 patients who will be divided into three groups, each group of at least 38 subjects, being able to overcome this value to assume the possible loss of follow-up.

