### Secondary objective

The secondary objective is to compare the respiratory effects obtained among patients affected by the coronavirus (COVID-19), after the application of a respiratory exercise program (REP), compared to those who perform a non-specific toning exercise program (NTEP) and a to sedentary control group performing a sham program, during the period of house confinement.

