### Statistical analysis

The statistical analysis will be carried out through the IBM-SPSS Statistics 24 software, considering the Kolmogorov-Smirnov test as the standard normality test. We will analyze the intragroup hypothesis contrast inference by Student’s *t* test for paired variables with parametric distributions and Kruskal-Wallis *H* for non-parametric distributions. We will analyze the intragroup hypothesis contrast inference by one-factor ANOVA in the case of parametric distributions and Kruskal-Wallis *H* for non-parametric distributions. We will apply a posteriori analysis (post hoc) through Bonferroni’s contrast for parametric distributions and Mann-Whitney’s *U* for non-parametric ones. The confidence level used will be 95% (0′05), and the power of the study will be 90% (0′1). If the rate of loss to follow-up were observed greater than 15%, we will perform an intention-to-treat analysis.

A sub-analysis will be carried out, depending on the age of the patients, sex, and autonomous community of residence.

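### Both objectives are respiratory, but the only power calculation is for fatigue and no outcome is named primary, so the stated 90% power does not extend to the respiratory question

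*Protocol article*

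**What the plan says.** The Primary objective section of the protocol article states: "The aim of our study is to analyze the respiratory effects of a therapeutic exercise program in patients affected by the coronavirus". The Secondary objective section is respiratory too: it compares the respiratory exercise programme (REP) with the toning programme (NTEP) and with the sham group (SP). Neither objective mentions fatigue.

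The section Sampling and sample size calculation derives the group size "based on the minimum clinically important differences in VASF". Outcome measures describes that scale as "Visual Analog Scale Fatigue (VASF), for fatigue measurement". The same section lists seven outcomes in sequence (VASF, FEV1, PEF, 6MWT, 30STST, MD12 and the Borg scale) and marks none as primary. On timing it says: "All outcomes will be measured daily using WhatsApp or by email for 21 days".

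The Statistical analysis section works at a 95% confidence level and says that "the power of the study will be 90" per cent, without naming an outcome. It plans a one-factor ANOVA or Kruskal-Wallis test, which I read as the between-group comparison. Post hoc contrasts follow, with Bonferroni in the parametric branch and Mann-Whitney in the other.

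**The concern.** The power statement should refer to the outcome that answers the primary question. Here the question is respiratory and the sizing outcome is fatigue, and the article does not connect the two. A reader of the final report could not tell which result was meant to decide the trial. The 90% would appear to support a respiratory conclusion for which no calculation was made.

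With seven unranked outcomes and no stated adjustment across them, whichever one reached significance could be presented as the answer. A chance finding would then be more likely than the nominal 5% suggests.

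**Working it through.** **1. The article's own figure.** Inputs from Sampling and sample size calculation: difference 0.10, SD 0.125 (standardised difference 0.10/0.125 = 0.8), alpha 0.05 one-sided, beta 0.10, losses 15%.

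n per group = 2 × [SD × (z₀.₉₅ + z₀.₉₀) / difference]² = 2 × [0.125 × (1.645 + 1.282) / 0.10]² = 26.8, so 27. With losses: 27 / 0.85 = 31.8, so 32. This is the stated figure. The two-sided version gives 32.8, so 33, and 33 / 0.85 = 38.8, so 39, which does not match. The 32 is therefore one one-sided, two-group comparison of VASF.

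**2. What the planned sample can detect on any outcome.** The article plans at least 38 per group; after 15% loss, 38 × 0.85 = 32.3, so about 32 are evaluable. Smallest standardised difference with 90% power at alpha 0.05 = (z_alpha + 1.282) × √(2/n):

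| n per group | one-sided | two-sided |
|---|---|---|
| 38 | 2.926 × 0.2294 = 0.67 | 3.242 × 0.2294 = 0.74 |
| 32 | 2.926 × 0.25 = 0.73 | 3.242 × 0.25 = 0.81 |

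**3. Power for a respiratory outcome.** The article gives no difference or SD for FEV1, PEF or MD12, so the effects below are assumptions. At 38 per group, power ≈ Φ(d × √(38/2) − z_alpha):

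| assumed d | one-sided | two-sided |
|---|---|---|
| 0.3 | 37% | 26% |
| 0.4 | 54% | 41% |
| 0.5 | 70% | 59% |
| 0.6 | 83% | 74% |
| 0.8 (the VASF assumption) | 97% | 94% |

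With 32 evaluable per group, d = 0.5 gives 64% / 52% and d = 0.8 gives 94% / 89%.

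**4. Error rate across seven outcomes, each tested at 5%.** If independent: 1 − 0.95⁷ = 0.302. With equally correlated normal test statistics (simulation, 400,000 draws, two-sided 5%), the chance of at least one false positive is:

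| assumed common correlation | family-wise error |
|---|---|
| 0.3 | 27% |
| 0.5 | 23% |
| 0.7 | 18% |
| 0.9 | 11% |

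The article reports no correlations between outcomes.

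**The case against.** Several stronger readings are tempting, and the article does not support them.

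- **That the trial is underpowered for respiratory outcomes.** No shortfall is shown. If the true respiratory effect is about 0.7 to 0.8 SD, the planned groups suffice. The power is unknown, not demonstrably low.
- **That type I error is wholly uncontrolled.** Group contrasts within an outcome carry Bonferroni in the parametric branch. The gap is across outcomes, and an analysis plan not shown here could still close it.
- **That each outcome is tested on each of 21 days.** Daily measurement is stated; daily testing is not. Sample selection speaks of measurements at the start, during and at the end, the paired t test fits a before-after comparison, and the missing Fig. 1 has a legend abbreviation for week. An error rate over 21 daily tests would describe an analysis nobody has planned.
- **That the error rate is 30%.** That figure needs independent outcomes, which is implausible: FEV1 and PEF come from the same device, and MD12 and Borg are recorded after the walk test. It is the upper end of a range.

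It can also be argued that fatigue is a declared interest. The abstract and Discussion name it beside exertion, physical health and respiratory activity, and VASF comes first in the outcome list. VASF might then be the implicit primary, or a document not shown might name another. Neither possibility removes the mismatch. If VASF is primary, it does not answer the stated objective; if a respiratory measure is primary, the calculation does not apply to it. Both the objective and the sizing basis are fixed in this article, so an unseen analysis plan cannot reconcile them.

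**Conclusion.** The point holds in this form: the objectives and the sizing outcome do not match, no primary outcome is named, and the 90% power is established for one one-sided VASF comparison at 0.8 SD only. For the respiratory objective, power is undetermined. It reaches 90% only for effects of at least 0.67–0.74 SD at 38 per group, or 0.73–0.81 SD with 32 evaluable, and nothing in the article says whether such effects are realistic.

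No adjustment across the seven outcomes is stated. At 5% each, the family-wise error is about 11–27% for common correlations of 0.9 to 0.3, with 30% as the independence limit. These rates rest on assumed equal correlations and on all seven outcomes being treated as co-equal, which is inferred from the absence of any ranking.

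**What to change.** Before any unblinded or comparative data are seen, and with the date of the decision recorded:

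- Name one primary outcome and time point that match the respiratory objective, for example FEV1 at the end of the 21 days, and tie it to the between-group contrasts in the Secondary objective section (REP against NTEP and against SP).
- Restate power as the standardised difference detectable with the evaluable patients, at the sidedness and significance level those contrasts will actually use. Limit the 90% statement to VASF.
- Make VASF and the remaining outcomes secondary with Holm adjustment, or label them exploratory.

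If VASF is kept as primary because it was the prespecified sizing outcome, say so openly and make the respiratory claims secondary. Rewording the objective to fatigue merely to fit the calculation would change the trial's question, so it should not be the default.

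Timing matters. Recruitment was set for 31 March to 30 April 2020, the Background cites figures of 24 May 2020, and the steering committee looks at ongoing results weekly. If those choosing the primary outcome have already seen comparative results, the choice should be reported as post hoc.

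The cost is wording: no extra patients or measurements. Claims on the non-primary outcomes become secondary, and the power statement becomes less favourable. Keeping all seven outcomes co-equal at alpha/7 would cost more. At 0.8 SD it needs 44 per group one-sided (44 / 0.85 = 51.8, so 52 with losses) or 50 two-sided (50 / 0.85 = 58.8, so 59), against the 38 planned.
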